# Use of biological mesh versus standard wound care in infected incisional ventral hernias, the SIMBIOSE study: a study protocol for a randomized multicenter controlled trial

**DOI:** 10.1186/1468-6708-14-131

**Published:** 2013-05-07

**Keywords:** Incisional ventral hernia, Infection, Biological mesh, Randomized trial

## Abstract

**Background:**

In infected incisional ventral hernias (IVHs), the use of a synthetic non-absorbable mesh is not recommended and biological meshes hold promise. However, the level of evidence for their safety and efficacy remains low.

**Methods:**

The SIMBIOSE trial is a multicenter, phase III, randomized, controlled trial comparing the use of a biological mesh versus traditional wound care in patients with an IVH. The primary end point is 6-month infectious and/or wound morbidity. Secondary end points are wound infection and recurrent hernia rates, post-operative pain, quality of life, time to heal, reoperation need, impact of the cross-linked mesh structure, and a medico-economic evaluation. One hundred patients need to be included.

**Results:**

The main results expected with biological mesh use are a significant decrease of post-operative morbidity, hernia recurrence, time to heal, and costs with an improved quality of life.

**Conclusions:**

For the first time, the impact of biological meshes in the treatment of IVHs will be evaluated in an academic, randomized, phase III trial to provide scientific evidence (
NCT01594450).

**Trial registration:**

ClinicalTrial.gov,
NCT01594450

## Background

Incisional ventral hernias (IVHs) occur in around 10% to 20% of patients after abdominal surgery
[1]. Their repair with a synthetic non-absorbable mesh to reinforce the abdominal wall leads to a significant decrease of nearly 50% in the hernia recurrence rate
[2-4].

However, synthetic non-absorbable meshes carry a risk of infection. A grading system has been published by the Ventral Hernia Working Group (VHWG), which can be used to assess the infection risk
[5] and to choose the ideal surgical procedure for the repair. The highest risk (Grade 4) occurs in ventral hernias that are characterized by active infection and septic dehiscence, especially if associated with an infected mesh, abscess or enterocutaneous fistula. In those patients, synthetic non-absorbable meshes are not recommended because of the high rates of mesh infection and the subsequent need for mesh removal and the consequent high rates of recurrence
[6].

This group of patients is difficult to manage because of the opposing objectives of treating the active infection and repairing the incisional hernia. Solely treating the active infection without a mesh puts the patient at risk of hernia recurrence, and the delayed placement of such a mesh does not protect against recurrent infection
[5]. As a result, the primary treatment of a ventral hernia in an infected field frequently requires the use of a synthetic absorbable mesh, with high recurrence rates due to rapid mesh reabsorption and a continued, albeit reduced, risk of mesh colonization and infection
[6]. Patients with an infected ventral hernia, whatever primary treatment is chosen, are subjected to repeated operations, prolonged treatment with significant costs, and an impaired quality of life
[7].

Biological meshes have been developed for these infrequent and difficult situations. They appear to be ideal in treating the incisional hernia and decreasing the risk of a colonizing infection. The non-human collagen matrix can support tissue regeneration through neovascularization and cell repopulation in a clinically acceptable timeframe and is resistant to infection
[5,8]. Biological meshes are recommended by the VHWG in infected fields, but the evidence for their systematic use remains low, due to the reported small patient series, a lack of long-term follow-up, the absence of substantive comparative studies, a high frequency of industrial study sponsors and there are no published, randomized controlled trials
[5]. Despite their high cost and the lack of evidence, the use of biological meshes in the treatment of infected incisional hernias has increased greatly in recent years. This has been in part due to the lack of a satisfactory alternative treatment for these difficult cases. Moreover, recent publications have given some of the limitations of bioprosthetic meshes, which have high rates of recurrent hernias
[9,10]. There is consequently an urgent need for a robust comparison of biological meshes with standard wound care for patients with an active infection of a incisional ventral hernia evaluating both patient and economic end points.

Consequently, we have designed an academic, large, multicenter, phase III, prospective, randomized, controlled trial comparing the use of a biological mesh versus standard wound care without a biological mesh in patients with an infected incisional ventral hernia, with an associated medico-economic evaluation, the SIMBIOSE trial.

## Methods/design

### Basic protocol overview

The SIMBIOSE trial is a large, multicenter, phase III, prospective, randomized, controlled, single-blinded trial comparing the use of a biological mesh versus traditional wound care without a biological mesh in patients with an infected incisional ventral hernia.

All patients will undergo an initial surgical procedure to treat the wound or intra-abdominal infection, and, either during the same procedure (single stage) or during a second later procedure within 1 month (double stage), repair the incisional ventral hernia.

Randomization is performed during the pre-operative consultation, after confirming the absence of contraindications to inclusion. Arm A patients undergo the implantation of a biological mesh (after debridement and treatment of the infection, either at the same time or within 1 month of randomization). Arm B patients undergo traditional wound care (debridement and treatment of infection), without the implantation of a biological mesh. For arm B, common wound care is used, following the normal practice of each surgeon. A biological mesh will not be placed within 6 months of randomization in this arm. Beyond this period, in the absence of wound healing, the treating surgeon may use a biological mesh as required.

Patients are blinded to the randomization arm during the first 6 months, which is until the evaluation of the primary end point.

To test the hypothesis that biological meshes will reduce abdominal complications, the two groups will be compared regarding their post-operative course and long-term follow-up including medical and economic end points.

This study is planned to last for 5 years, with a 2-year inclusion period and a 3-year follow-up period. The results for the primary end point will be available 6 months after the end of the inclusion period (2 years).

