### Criteria for evaluation of trial objectives

The primary objective will be assessed by the proportion of patients experiencing at least one morbid wound event within 6 months of surgery. Such morbidity includes infectious morbidity (superficial, deep or systemic) and/or wound morbidity (wound dehiscence or recurrence of incisional hernia).

Superficial complications include hematoma or seroma formation, wound abscesses or other problems with wound healing. Wound complications include wound dehiscence, recurrent hernias, mesh infection or associated hematoma. The development of an enterocutaneous fistula, intra-abdominal abscess, peritonitis or intestinal occlusion will be recorded as manifestations of intra-abdominal complications. Other complications of a general nature, including respiratory, cardiac, thromboembolic, septic and immune- or allergy-mediated morbidity, will also be recorded.

A standardized definition of all complications has been given in detail in the protocol to allow uniform reporting.

To evaluate the secondary objectives the following criteria will be evaluated: (i) the proportion of patients with a wound infection at 45 days, 3 months and 1 year after the initial operation; (ii) the proportion of patients with a recurrent hernia on clinical examination 1, 2 and 3 years postoperatively, or on computed tomography (CT) examination 3 years postoperatively; (iii) the proportion of patients suffering post-operative pain at 45 days, 3 and 6 months, and 1, 2 and 3 years as assessed by an analog visual scale and analgesic consumption; (iv) patients’ quality of life using EuroQol 5D, SF-12 and the Carolinas comfort scale (CCS) at 45 days, 3 and 6 months, and 1, 2 and 3 years postoperatively; (v) time to heal, measured between patient randomization and complete wound healing; (vi) the proportion of patients requiring a surgical procedure for a wound event (infection or hernia recurrence) 6 months after randomization, and the number of such surgical procedures; (vii) comparison of cross-linked and non-cross-linked meshes; (viii) medico-economic evaluation at 6 months; (ix) cumulative length of hospital of stay; (x) number of medical consultations; (xi) number of day-case admissions and (xii) related medications taking into account number of prescriptions and amount of drug prescribed.

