#### Post-operative period

All patients will benefit from the usual standards of post-operative care. Additional surgical procedures will be performed as required. Other treatments such as negative pressure wound therapy or autologous skin grafting may be used, regardless of the randomization arm.

In arm B, for ethical considerations, after the evaluation of the primary end point at 6 months, in the absence of wound healing and/or persistence of infection, the use of a biological mesh will be possible – if judged necessary by the treating surgeon.

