### Data collection and follow-up

The patients will be followed-up at 45 days, 3 and 6 months, and 1, 2 and 3 years after randomization. The follow-up protocol includes a physical examination to assess wound events, wound pain, patient temperature and adverse events, and a biological investigation (leukocyte count and C-reactive protein). At 6 months and 3 years, a CT scan and a bacteriological investigation are mandatory. These investigations may be performed at any other consultation according to clinical requirements. The quality of life questionnaires EuroQol 5D, SF-12 and CCS will be completed by the patient at each stage of the 3 years of follow-up. The necessity for follow-up beyond the scheduled formal consultations will depend upon the surgeon’s clinical judgment. All events and additional costs will be listed.

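### Only the patient is blinded; no masking of the examination-based primary endpoint is described, so the main comparison is open to detection bias, most plausibly toward the mesh

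*Protocol article*

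**What the plan says.** All references are to the Methods/design part of the protocol article.

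- **Who is blinded.** Basic protocol overview calls the study a "prospective, randomized, controlled, single-blinded trial comparing the use of a biological mesh versus traditional wound care" and then names the blinded party: "Patients are blinded to the randomization arm during the first 6 months, which is until the evaluation of the primary end point". The Randomization section repeats this. No other party is described as blinded.
- **What is scored.** Criteria for evaluation of trial objectives defines the primary endpoint as "the proportion of patients experiencing at least one morbid wound event within 6 months of surgery", covering infectious morbidity and wound morbidity (dehiscence or recurrence). The next paragraph describes the complications in more detail, for example: "Superficial complications include hematoma or seroma formation, wound abscesses or other problems with wound healing".
- **How it is found.** Data collection and follow-up states: "The follow-up protocol includes a physical examination to assess wound events, wound pain, patient temperature and adverse events". It adds: "At 6 months and 3 years, a CT scan and a bacteriological investigation are mandatory". It does not say who examines, or that the examination or the CT reading is masked.
- **Safeguards stated.** "A standardized definition of all complications has been given in detail in the protocol to allow uniform reporting". Under Funding, ethics and safety, an independent DSMB evaluates the primary endpoint data in confidence.
- **Mesh access in arm B.** A biological mesh is withheld for 6 months. For the time after the endpoint evaluation, the Post-operative period section leaves the decision to the surgeon: "in the absence of wound healing and/or persistence of infection, the use of a biological mesh will be possible – if judged necessary by the treating" (the quote stops just before the sentence ends). Basic protocol overview and Randomization state the condition in slightly different terms (no wound healing; treatment failure).

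**The concern.** A blind guards an endpoint best when it covers whoever measures it. Here the blind ends at the primary evaluation, which presents it as serving that evaluation. But the endpoint is recorded at examination and is not reported by the patient. The operating surgeon implants or withholds the mesh and so knows the arm, and nothing shown separates that knowledge from the scoring.

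The endpoint is also sensitive to small differences in scoring. One call is enough to make a patient an event, and superficial infection, dehiscence and clinical recurrence all have borderline presentations. The abstract expects a significant fall in morbidity with the mesh. If that expectation affects borderline calls, it acts toward more events in arm B and fewer in arm A.

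The later access to a biological mesh in arm B adds an indirect incentive. Its conditions overlap the endpoint in content and are judged at about the same time.

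At stake is whether a significant primary result could be told apart from a difference in scoring.

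**Working it through.** **1. The plan's own figure.** Inputs from Statistical evaluation and sample size: 60% in arm B, 30% in arm A, two-sided α = 0.05, power 80%.

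n = [1.960·√(2·0.45·0.55) + 0.842·√(0.6·0.4 + 0.3·0.7)]² / 0.30² = 41.97, so 42 per group.

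With continuity correction: (41.97/4)·[1 + √(1 + 4/(41.97·0.30))]² = 48.4, so 49 per group.

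The stated 49 is reproduced. The 100 planned patients are taken as 50 per arm.

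**2. What is assumed.** The article gives no misclassification rates, so every rate below is an assumption. Let p be the true event rate in both arms (no effect), u the share of event-free arm B patients scored as events, and d the share of arm A events missed.

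- Observed rate in B = p + u(1 − p)
- Observed rate in A = p(1 − d)

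For p = 45%, midway between the planning rates, and u = d = 10%:

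- B: 0.45 + 0.10·0.55 = 50.5%. On average this is 50·0.055 = 2.75 patients over-called.
- A: 0.45·0.90 = 40.5%. On average this is 50·0.045 = 2.25 patients missed.

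**3. Chance of a significant result favouring the mesh.** Exact binomial enumeration over all pairs of counts, uncorrected Pearson chi-squared at two-sided 5%, counting only results with more events in B:

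| Assumed scoring error | p = 30% | p = 45% | p = 60% |
|---|---|---|---|
| None | 2.5% | 2.8% | 2.6% |
| 10% over-called in B only | 11.0% | 8.8% | 6.2% |
| 10% over-called in B and 10% missed in A | 18.5% | 18.2% | 18.0% |
| 20% over-called in B only | 30.7% | 21.1% | 12.9% |
| 20% over-called in B and 20% missed in A | 56.3% | 54.3% | 54.4% |

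The plan also allows Fisher's exact test. With it, the p = 45% values are 1.7% with no error, 6.0% with 10% in B only, and 13.3% with 10% both ways.

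**4. How many calls are needed.** From equal counts of 15, 22, 25 or 30 events per arm, 10 extra calls in arm B are the fewest that reach significance. For 32 v 22: χ² = 0.20² / (0.54·0.46·2/50) = 4.03, above 3.84. With 9 extra calls (31 v 22), χ² = 3.25.

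**5. The endpoint and the arm B condition side by side.**

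| | Primary endpoint | Later mesh in arm B |
|---|---|---|
| Window | any time within 6 months of surgery | state at 6 months |
| Content | any qualifying event, including one that has resolved | no healing, persistent infection or treatment failure |
| Order | first | after the endpoint evaluation |

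An early event that resolves counts for the endpoint but does not meet the condition. The two overlap without being the same judgment.

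**The case against.** The strongest reply is that the article condenses a full protocol. That protocol holds the detailed complication definitions and may name a masked assessor. The article never says that the treating surgeon scores the endpoint; that is an inference. This stands, and the sponsor could settle the point by citing such a provision. But who is blinded is a design feature that the article does state, and as stated it covers only the patient.

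Several further points limit the concern:

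- **Existing safeguards.** Standardized definitions, the mandatory 6-month CT and bacteriology, and the DSMB's confidential review all narrow discretion. None is described as masked assessment, and definitions govern how findings are classified more than what an examiner records.
- **Direction.** A reader might infer that the comparison is biased toward the mesh. The article does not show this. Mesh infection is a listed complication that could count against arm A, and the Background reports high recurrence with biological meshes.
- **Incentive.** A reader might also infer that recording an event is what opens access to a mesh in arm B. No section says so. Access rests on clinical state and surgeon judgment and comes after the endpoint evaluation, and additional procedures are allowed as required without restriction to one arm.
- **Soft items.** Seroma and residual healing problems are listed in the paragraph after the endpoint definition, alongside general complications, so their place in the primary endpoint is not explicit. The items in the definition itself still need judgment.
- **Value of the patient blind.** It is not worthless. It can affect symptom reporting, unscheduled attendance and retention.

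**Conclusion.** The point holds in limited form. The only blind described is the patient's, the endpoint is identified at examination and depends partly on judgment, and no masking of its assessment is described. The primary comparison is therefore open to detection bias, most plausibly toward the mesh. Actual bias, its size and its direction cannot be established from the article.

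At a true rate of 45% in both arms, an assumed 10% over-calling in arm B alone takes the one-directional error from 2.8% to 8.8%. The 18% figure needs opposite errors in both arms, and the arm B mesh access could not explain the arm A part of it. Fisher's test gives lower figures. These values show how sensitive the result is to scoring; they do not predict what will happen.

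The planned sample size is unaffected. This is a worthwhile and inexpensive improvement, and it does not show the design to be invalid.

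**What to change.** 1. **State who scores the 6-month endpoint**, and do not present the patient blind as masking of that assessment.
2. **Mask the CT reading.** The usual site radiologist reads the mandatory 6-month CT with the allocation left off the request. Recurrence or collection for the endpoint is taken from that report.
3. **Lock the 6-month endpoint page** before any arm B decision on a biological mesh is recorded. This makes the order already implied in the Post-operative period section auditable. It concerns data entry only and changes no clinical rule.
4. **Add a sensitivity analysis** of the primary comparison, restricted to the components least dependent on unmasked judgment: CT-documented recurrence or abscess, and positive culture. Say that reoperation and treatment decisions remain unmasked.
5. **Where an existing body can do it without extra staff**, classify events from records with the arm removed. The article describes no such committee besides the DSMB, so the fix should not depend on this step.

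**Cost.** A short amendment, a revised CT request form, a lock on one data page and one extra analysis. No new visit, procedure or patient. With 41 of 100 patients enrolled at publication, most of the trial could still benefit.

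**Limits.** Masking fails where the mesh is visible on CT or revealed in the record, and desk classification cannot correct what an unmasked examiner entered.

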### Objectives

The primary objective is to compare the effect of two therapeutic strategies in the treatment of infected ventral hernias on 6-month infectious and/or wound post-operative morbidity. The two strategies for comparison are the use of a biological mesh versus standard wound care without a biological mesh.

Secondary objectives are the assessment of (i) wound infection rates at 45 days, 3 months and 1 year, (ii) recurrent hernia rates at 1, 2 and 3 years, (iii) post-operative pain, (iv) quality of life, (v) time to heal, (vi) need for wound reoperation due to infection or hernia recurrence, (vii) impact of the cross-linked mesh structure on (a) the primary objective, (b) the 1-year infection rate and (c) 1- and 3-year recurrence rates, (viii) medico-economic evaluation taking into account the direct costs of infected ventral hernia treatment.

### Inclusion criteria

The study includes patients with an active infection of an incisional abdominal wall hernia.

The inclusion criteria are that patients: (i) have a wound infection related to a synthetic non-absorbable mesh of at least 15 days’ duration, (ii) have an incisional abdominal hernia with an abscess or fistula, without the presence of a synthetic non-absorbable mesh, (iii) have an incisional abdominal hernia smaller than 20 cm for the two largest diameters, (iv) have an incisional abdominal hernia requiring surgical repair, (v) have an incisional abdominal hernia amenable to repair with a single biological mesh, (vi) are aged over 18, (vii) have signed written informed consent, and (viii) are entitled to care within the French national public health-care system.

### Exclusion criteria

The general exclusion criteria are the common contraindications for surgery, depending on patient, disease or operative technique. Specifically, exclusion criteria are that patients: (i) do not have an infected incisional abdominal hernia, (ii) have a history of biological mesh placement, (iii) have an incisional abdominal hernia in a contaminated but uninfected field (stoma presence, violation of gastrointestinal tract, or defined as grade 3 by the VHWG), (iv) have an incisional abdominal hernia larger than 20 × 20 cm, (v) have a body mass index ≥ 40 kg/m^2^, (vi) score 4 or 5 on the American Society of Anesthesiologists scale, (vii) have immunosuppression, including ongoing steroid and cytotoxic therapy, (viii) have a chronic disease such as cirrhosis, renal insufficiency with renal dialysis, malignant disease or a known collagen disorder, (ix) have a life expectancy less than 36 months, (x) are allergic to one of the biological mesh components, (xi) are pregnant or breastfeeding, (xii) have refused to participate, (xiii) are non-compliant or (xiv) suffer from legal incapacity.

### Criteria for evaluation of trial objectives

The primary objective will be assessed by the proportion of patients experiencing at least one morbid wound event within 6 months of surgery. Such morbidity includes infectious morbidity (superficial, deep or systemic) and/or wound morbidity (wound dehiscence or recurrence of incisional hernia).

Superficial complications include hematoma or seroma formation, wound abscesses or other problems with wound healing. Wound complications include wound dehiscence, recurrent hernias, mesh infection or associated hematoma. The development of an enterocutaneous fistula, intra-abdominal abscess, peritonitis or intestinal occlusion will be recorded as manifestations of intra-abdominal complications. Other complications of a general nature, including respiratory, cardiac, thromboembolic, septic and immune- or allergy-mediated morbidity, will also be recorded.

A standardized definition of all complications has been given in detail in the protocol to allow uniform reporting.

To evaluate the secondary objectives the following criteria will be evaluated: (i) the proportion of patients with a wound infection at 45 days, 3 months and 1 year after the initial operation; (ii) the proportion of patients with a recurrent hernia on clinical examination 1, 2 and 3 years postoperatively, or on computed tomography (CT) examination 3 years postoperatively; (iii) the proportion of patients suffering post-operative pain at 45 days, 3 and 6 months, and 1, 2 and 3 years as assessed by an analog visual scale and analgesic consumption; (iv) patients’ quality of life using EuroQol 5D, SF-12 and the Carolinas comfort scale (CCS) at 45 days, 3 and 6 months, and 1, 2 and 3 years postoperatively; (v) time to heal, measured between patient randomization and complete wound healing; (vi) the proportion of patients requiring a surgical procedure for a wound event (infection or hernia recurrence) 6 months after randomization, and the number of such surgical procedures; (vii) comparison of cross-linked and non-cross-linked meshes; (viii) medico-economic evaluation at 6 months; (ix) cumulative length of hospital of stay; (x) number of medical consultations; (xi) number of day-case admissions and (xii) related medications taking into account number of prescriptions and amount of drug prescribed.

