### Treatment methods

In both arms, surgical procedures should be performed within 30 days of randomization. Irrespective of randomization, the surgery may be performed in one or two steps at the surgeon’s discretion.

For both arms, after excision of the infected wound (as necessary) and intra-abdominal adhesiolysis, an extensive debridement of all infected structures, such as mesh, soft tissues, abscess or fistula, will be performed, aiming to reduce the bacterial load as much as possible. After bacteriological sampling, if a synthetic, non-absorbable mesh is present it will be completely excised, which treats the underlying cause of infection. The abdominal cavity will be lavaged with normal saline.

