#### Arm A

A measurement of the two largest diameters of the incisional ventral hernia will be performed, in order to choose the most appropriate size of biological mesh. Intra-operatively the surgeon will decide whether to perform a single-stage procedure, with immediate implantation of the biological mesh, or a two-stage procedure, with a delayed implantation of the biological mesh within the following 30 days.

The biological mesh will be placed in an underlay position, that is, either intra-abdominal or pre-peritoneal retro-muscular, under the appropriate tension, to help prevent the development of laxity. The surgeon is free to choose the biological mesh from among the five biological meshes with a CE mark presently available in France: Collamend FM® (Davol), Strattice® (Lifecell), Tutomesh® (Tutogen), Surgisis® (Cook) and Permacol® (Covidien).

Regardless of placement, the mesh must overlap the intact fascia by at least 3 cm to 5 cm. The mesh fixation will be performed using a monofilament, non-absorbable, polypropylene suture. Where possible, a tension-free closure of the fascia will be performed. Only if fascia closure is impossible, will a bridging repair be used, that is, without a fascia overlay.

Drainage and skin closure will be performed according to the surgeon’s choice.

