### Statistical evaluation and sample size

The hypothesis of this phase III study is that the use of a biological mesh in infected incisional hernias will reduce wound morbidity within 6 months.

The sample size was calculated using the difference in the primary end point of morbidity, which is expected to be 60% in arm B
[11-13] and 30% in arm A.

To demonstrate this difference of 30%, using α = 0.05 and β = 0.20, and according to the chi-squared test, the sample size required in each group is 49. This is based on a two-sided significance level (alpha) of 0.05 and a power of 80%. Since we estimate that very few patients will be lost to follow-up because of the short time-scale for the primary end point (6 months), we consequently plan to include 100 patients in this study.

The statistical evaluation will be based for the primary end point on the intention-to-treat analysis set, using a chi-squared test or the Fisher’s exact test. Statistical analysis will be performed with the SAS software version 9.2.

This study is planned to last for 5 years, with a 2-year inclusion period and a 3-year follow-up period; we expect that two patients will be included per year for each participating center. The results for the primary end point will be available 6 months after the end of the inclusion period (2 years).

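### The primary endpoint window runs from surgery, but its 6-month assessment and the arm B mesh restriction run from randomization, so up to 16.4% of the window falls after both

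*Protocol article*

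**What the plan says.** All references are to the protocol article.

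- **Endpoint clock: surgery.** Criteria for evaluation of trial objectives: "the proportion of patients experiencing at least one morbid wound event within 6 months of surgery".
- **Visit clock: randomization.** Data collection and follow-up: "The patients will be followed-up at 45 days, 3 and 6 months, and 1, 2 and 3 years after randomization". The same section adds: "At 6 months and 3 years, a CT scan and a bacteriological investigation are mandatory".
- **Arm B restriction: randomization.** Basic protocol overview: "A biological mesh will not be placed within 6 months of randomization in this arm", followed by "Beyond this period, in the absence of wound healing, the treating surgeon may use a biological mesh as required". The Randomization section uses the same origin.
- **Delay allowed before surgery.** Treatment methods, for both arms: "surgical procedures should be performed within 30 days of randomization".
- **Results date.** Statistical evaluation and sample size: "The results for the primary end point will be available 6 months after the end of the inclusion period".
- **Second stage.** The Arm A section allows "a delayed implantation of the biological mesh within the following 30 days", whereas Basic protocol overview and Randomization place arm A implantation no later than one month from randomization.

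**The concern.** Unless a patient is operated on the day of randomization, the endpoint window closes after the visit meant to assess it. The last part of the window then has no scheduled CT, although recurrent hernia is a component of the endpoint and the next mandatory CT is at 3 years. In arm B the same part of the window lies in the period when a biological mesh may be used.

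Two analysts could therefore count different events from the same data. One would stop at the 6-month visit; the other would add events up to 6 months after the operation. If this is not settled beforehand, the choice could be made after the data are seen.

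The mention of surgery cannot be dismissed as shorthand for a single clock. The same section counts wound infection from the initial operation, but time to heal and reoperation from randomization.

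**Working it through.** **1. The plan's own figure.** Inputs from Statistical evaluation and sample size: 60% in arm B, 30% in arm A, two-sided α = 0.05, power 80%.

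- Without continuity correction: n = [1.960·√(2·0.45·0.55) + 0.842·√(0.6·0.4 + 0.3·0.7)]² / 0.30², which rounds up to 42 per group.
- With continuity correction: n′ = (n/4)·[1 + √(1 + 4/(n·0.30))]², which rounds up to 49 per group.

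The stated 49 is reproduced with the correction. It does not depend on where the 6-month clock starts, so aligning the clocks leaves it, and the planned 100, unchanged.

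**2. Size of the gap.** Take 6 months as 365.25/2 = 182.6 days. For a patient operated on day g after randomization, the visit falls at day 182.6 and the window closes at day 182.6 + g. The share of the window after the visit is g/182.6. The arm B restriction ends on the same day as the visit, so the same share follows it.

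- g = 0: 0%
- g = 7: 3.8%
- g = 15: 8.2%
- g = 30, the limit in Treatment methods: 16.4%

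**3. Results date.** A patient included on the last day of inclusion and operated on day 30 has a window that closes 30 days after the point at which primary results are due.

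**4. A ceiling on the effect (illustration only).** Assume that every patient has the same g, that the hazard is constant within each arm, and that every event after the visit is lost. The observed rate is then 1 − (1 − p)^f, with f = (182.6 − g)/182.6. Power is for the uncorrected chi-squared test with 50 per group.

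| g (days) | Arm B | Arm A | Power |
|---|---|---|---|
| 0 | 60.0% | 30.0% | 86.6% |
| 7 | 58.6% | 29.0% | 85.6% |
| 15 | 56.9% | 27.9% | 84.5% |
| 30 | 53.5% | 25.8% | 81.9% |

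The largest loss is 86.6 − 81.9 = 4.7 percentage points. These powers should be compared with the uncorrected 86.6%, not with the plan's 80%, which comes from the corrected formula.

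**5. Loosest reading of the second-stage wording.** If a first operation on day 30 could be followed by implantation 30 days later, and if the clock started at that second stage, g would be 60 and the share 60/182.6 = 32.9%. This needs both delays at their maximum, and it goes against the one-month limit stated in the other two sections.

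**The case against.** The strongest reply is that this is loose wording with little consequence. Much of that stands.

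- **Late events need not be lost.** Data collection and follow-up allows CT and bacteriology at any other consultation when clinically required, allows extra follow-up, has a 1-year visit and requires all events to be listed. What the tail of the window lacks is the mandatory assessment, not all observation. The 16.4% is also a share of time at the longest delay, not a share of events.
- **Crossover is restricted.** After 6 months, arm B may receive a biological mesh only for non-healing, persistent infection or treatment failure. Most such patients would already count as events in a binary endpoint. The Post-operative period section also places that use after the primary evaluation. This would remove the overlap if the evaluation were timed from surgery, but the only scheduled 6-month evaluation is timed from randomization.
- **The full protocol may say more.** The article refers to standardized complication definitions given there. The index operation in staged repairs and the handling of never-operated patients may be settled in it, so their absence here is not a separate fault.

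A reader might draw two stronger conclusions that the article does not support. One is that the tail of the window is stated to be unblinded. Patient blinding covers the first 6 months up to the primary evaluation, with no origin named; randomization is only implied. The other is that staging favours the mesh because only arm A could lose events between stages. Basic protocol overview and Treatment methods allow one or two stages in both arms, and no section starts the clock at the second stage. Any figure for such a bias would need inputs that the article does not give.

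The reply does not remove the contradiction itself. The article gives two closing dates for the primary endpoint and does not choose between them.

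**Conclusion.** The point holds as a mismatch of time origins in the definition of the primary endpoint. Followed as written, 0 to 30 days, and at most 16.4% of the window, lie after the scheduled assessment and after the arm B restriction ends. For late-included patients the window can outlast the stated results date. This rests on the 30-day limit for surgery and on a 6-month visit held on time.

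The practical effect is modest. Even under the extreme assumptions in the working (all patients at 30 days, constant hazard, all later events lost), power falls by 4.7 points, and the sample size does not change. The 32.9% figure is only what the loosest reading of the Arm A section would imply and should not be taken as the expected gap. The documents support no claim of bias in a particular direction. The wording still needs correction because it decides which events count in the primary analysis.

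**What to change.** Amend the endpoint definition and carry it into the analysis plan:

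1. Close the primary window, for every randomized patient in both arms, at the 6-month visit counted from randomization.
2. Count post-operative events from the initial operation, whatever the number of stages.
3. Keep never-operated patients in the intention-to-treat denominator with the same closing date, and state how an event is counted in a patient with no operation date.
4. Report time from randomization to first operation by arm.
5. Add a sensitivity analysis of events within 6 months of the initial operation, using events recorded at any visit.

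This definition still opens at the operation and closes by reference to randomization, and the text should say so. What it gains is a closing date that coincides with the mandatory assessment, the end of the arm B restriction as stated, and the announced results date.

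The cost is a wording change, with no new visit or patient. The downside is that late-operated patients contribute up to 30 days less post-operative exposure to the primary analysis, which items 4 and 5 make visible.

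Separately, the clinical team must reconcile the second-stage timing in the Arm A section with Basic protocol overview, Randomization and Treatment methods. This review takes no position on which is right.
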